However, a burgeoning literature suggests that camouflaging may be a risk factor for depression and anxiety in autism [25, 37, 53–57], irrespective of gender [58]. Interestingly, Cage and colleagues [37] suggest that camouflaging may mediate the relationship between social stressors (e.g., lack of autism acceptance, bullying) and anxiety and depression. That is, those who experience more social stressors (such as a lack of autism acceptance) are more likely to camouflage their autistic traits, which in turn results in higher levels of anxiety and depression. However, a recent study found that whilst autism-related stigma was associated with lower wellbeing, camouflaging did not mediate this relationship (despite camouflaging being positively associated with autism-related stigma; [59]). Future research should verify whether camouflaging mediates the relationship between autism acceptance/stigma and anxiety and depression more specifically.

It is important to note that the terms we use to refer to camouflaging vary across the globe [60]. In Japan, the term ‘over-adaptation’ is used to describe excessive efforts made by people (i.e., society more broadly) to meet external demands and expectations, even if this means forcibly suppressing their internal needs [61]. In recent years, this term has been applied to autism to describe the substantial efforts made by autistic people to fit into an environment as a result of differences in interpersonal and social behaviour [62–64]. As such, this concept is highly similar to the construct of camouflaging (see [61] for a discussion around the similarities and differences between the constructs of camouflaging and over-adaptation in autism). Importantly, there is anecdotal evidence that over-adapatation is associated with poorer mental health in autistic individuals in Japan [65]. However, to date no empirical studies have tested this relationship [61], and therefore further study of over-adaptation and camouflaging in Japan is necessary.

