#### 1.1.3. The current study

In the current study, we aim to replicate the regression analyses from previous research that found a) depression was predicted by external and personal acceptance, and stress was predicted by external acceptance [37], b) camouflaging was predicted by stigma [59], and c) anxiety was predicted by camouflaging [58] (whilst controlling for relevant participant characteristics, e.g., age, gender, etc.) in a more representative sample of autistic adults. In addition, we aim to compare autistic individuals’ experiences of autism acceptance, camouflaging and mental health across multiple countries: Australia, Belgium, Canada, Japan, South Africa, the United Kingdom, and the United States. Importantly, exploring these factors across cultures has the potential to a) elucidate the potential routes to greater autism acceptance, reduced need for camouflaging behaviours and improved mental health outcomes, b) identify ‘priority regions’ for anti-stigma interventions (like those in Ranson and Byrne, [81] and Gillespie-Lynch et al., [82]), and c) highlight areas where greater support for mental health difficulties is needed. In addition, since acceptance is likely to vary across cultures, we are employing an experimental design which naturally maximises variation in autism acceptance, thus giving us the ability to more sensitively assess the impact of autism acceptance on camouflaging and mental health respectively.

In order to fulfil our aims, participants will complete a number of questionnaires including Autism Acceptance Questions [37], the Camouflaging Autistic Traits Questionnaire [51], and the 21-item Depression, Anxiety and Stress Scale (DASS-21; [83]). Participants will also provide demographic information (e.g., age, sex assigned at birth, gender identity, sexual identity, ethnicities, country of birth, country of residence, years lived in country of residence, number of siblings, level of education, income, autism diagnosis, person/team that gave them their diagnosis, age of autism diagnosis, co-occuring diagnoses, how verbal they would consider themselves now, and how verbal they were as a child).

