### 2.1. Study type (required)

Observational Study—Data is collected from study subjects that are not randomly assigned to a treatment. This includes surveys, natural experiments and regression discontinuity designs.

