#### 4.2.4. Depression, anxiety and stress

To measure levels of depression, anxiety and stress, we will use the Depression, Anxiety and Stress Scale (DASS-21; [83]). In this 21-item questionnaire, participants judge whether certain statements (e.g., “I found it hard to wind down”) could be applied to their life over the past week on a scale from one to four (1 = “did not apply to me at all; 2 = “applied to me some of the time”; 3 = “applied to me a considerable degree”; 4 = “applied to me very much or most of the time”). The 21 items can be reduced to 7 items each for the depression, anxiety and stress subscales. Total scores for each subscale are calculated and multiplied by two (meaning that scores for each subscale range from 14 to 42), with higher scores representing higher depression, anxiety and stress. The DASS-21 has been previously used with autistic participants (e.g., [37, 89]) and the English [37, 89], French [90], and Japanese [91] versions have good internal consistency and factor validity.

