Moreover, in order to investigate whether camouflaging mediates any relationships we identify between autism acceptance and mental health outcomes, we will complete mediation analyses. There are several methods used to test the statistical significance of mediated effects [104–106]. In the present study, we will use structural equation modelling (SEM), a powerful statistical technique used to infer causal relationships between variables, for our mediation analyses. We decided to use SEM over standard regression methods (as outlined by Baron and Kenny; [107]) as this technique is regarded as “a more appropriate inference framework for mediation analyses” (see [108]). In addition, we will use bias-corrected bootstrapping to create confidence intervals as there is a consensus that it is the most powerful method for testing mediated effects [104, 109–112]. Whilst we believe that there will be sufficient statistical power to detect an effect, we may supplement this analysis with Bayesian mediation analyses if it appears that we are underpowered.

In addition, we will calculate standardised residuals for the relationships between autism acceptance and mental health, autism acceptance and camouflaging, and camouflaging and mental health, for all participants. Then we will complete an exploratory MANOVAs in which we will compare the standardised residuals across countries. This will allow us to compare the strength of these relationships in each of the countries by comparing the levels of unexplained variance following regression analyses. This is useful because the strengths of these relationships could, in principle, vary across our countries. For example, it could be that in collectivist, relative to individualistic, cultures, camouflaging accounts for a smaller portion of variance in mental health as hiding any traits that deviate from the norm is common (and therefore may not be detrimental to mental health).

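### The exploratory mediation analysis presents SEM as a route to causal inference, which a non-randomised survey with no repeat measurement cannot support

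*Protocol article*

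**What the plan says.** Section 5.6 (Exploratory analysis) gives the question: "in order to investigate whether camouflaging mediates any relationships we identify between autism acceptance and mental health outcomes, we will complete mediation analyses". For the method it says "we will use structural equation modelling (SEM), a powerful statistical technique used to infer causal relationships between variables, for our mediation analyses", with bias-corrected bootstrap confidence intervals.

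The assumed order comes from section 1.1.1. It explains a cited suggestion that people facing more social stressors are "more likely to camouflage their autistic traits, which in turn results in higher levels of anxiety and depression". The same section then reports a study in which camouflaging did not mediate, and calls for the question to be checked.

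The design is given in three places:
- Section 2.1: "Data is collected from study subjects that are not randomly assigned to a treatment. This includes surveys". Section 2.4 confirms that nothing is randomised.
- Section 1.1.3: "participants will complete a number of questionnaires including Autism Acceptance Questions", together with the CAT-Q and the DASS-21. No repeat measurement is described.
- Section 4.2.4: the DASS-21 asks whether statements "could be applied to their life over the past week". One acceptance item in section 4.2.2 uses the same one-week window.

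Section 1.1.3 adds that variation in acceptance between countries will let the authors "more sensitively assess the impact of autism acceptance on camouflaging and mental health respectively".

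**The concern.** SEM estimates the paths of an order that the analyst has chosen. It does not supply the time order or the control of confounding that the design lacks. Someone who is depressed or anxious in a given week may camouflage more and also feel less accepted. That account can produce the same correlations as the planned one. The overlapping recall windows do not help to separate them.

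The article is not settled on direction for one of these paths. Section 3.4.1 describes the basis for 286 participants as anxiety explaining variance in camouflaging, while section 5.1.1 models anxiety as the outcome of camouflaging.

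At stake is how a significant indirect effect may be read. The hopes stated in section 1.1.3, of finding routes to less camouflaging and better mental health, depend on direction. A reader told that the method infers causation could take a directional conclusion that these data cannot give.

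**Working it through.** **Plan's own figure.** The article gives no sample size, power or path size for the mediation analysis, so there is none to reproduce. The n used here is the study minimum of 286 (sections 3.3 and 3.4.1), which was set for the regressions. All link sizes below are assumptions.

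**Notation.** X = acceptance, M = camouflaging, Y = mental health score, all standardised.

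**Step 1: fit.** Three variables have three correlations. A mediation model with a direct path has three paths (a, b, c). It is saturated and fits perfectly in any order, so fit cannot choose between orders.

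**Step 2: indirect effects from the correlations.**
- Planned order X→M→Y: r_XM × (r_MY − r_XM·r_XY) / (1 − r_XM²)
- Reversed order Y→M→X: r_MY × (r_XM − r_MY·r_XY) / (1 − r_MY²)

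**Step 3: pure chain, equal links, no direct path.** With links −0.25 and 0.25, r_XY = −0.0625. Both formulas give −0.0625. The forward and reversed chains imply the same correlation matrix, so the planned model performs alike under either.

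**Step 4: distress drives both.** Let Y cause X (−0.4) and M (0.20, 0.25 or 0.30), with no effect of M on Y. For 0.25: r_XM = −0.4 × 0.25 = −0.10. The planned effect is −0.10 × (0.25 − 0.04)/0.99 = −0.021, although no mediation exists.

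**Step 5: detection at n = 286.** Simulated data sets, with both paths tested at .05:

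| Truth | Links 0.20 / 0.25 / 0.30: planned order significant |
|---|---|
| Reversed pure chain | 86% / 98% / 99.5% |
| Distress drives X and M | 24% / 39% / 54% |

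Repeat runs moved these by about two percentage points at most.

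**Step 6: planned order true, with a direct path c = −0.3.** Here r_XY = c + ab and r_MY = b + ac. For a = −0.20 and b = 0.30: r_XY = −0.36 and r_MY = 0.36. The reversed effect is 0.36 × (−0.20 + 0.1296)/0.8704 = −0.029, against −0.060 in the planned order.

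| a, b | Planned significant | Reversed significant |
|---|---|---|
| −0.20, 0.30 | 93% | 27% |
| −0.15, 0.35 | 71% | 6% |
| −0.35, 0.15 | 71% | 99% |

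**Step 7: the interval actually planned.** Bias-corrected bootstrap, 95% level assumed, 200 data sets of 286 with 500 draws each:
- True order Y→M→X: the planned model was significant in 74% (with a direct path) to 98% (pure chain).
- Only an unmeasured common cause, loadings of 0.5 in absolute size on all three variables: 96%.

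**Step 8: how much confounding is enough.** In the linear model the indirect effect vanishes when the correlation between the mediator and outcome residuals equals the partial correlation of M and Y given X: (r_MY − r_XM·r_XY) / √[(1 − r_XM²)(1 − r_XY²)]. For the pure chain with link 0.20 this is (0.20 − 0.008)/√(0.96 × 0.9984) = 0.196. With link 0.30 it is (0.30 − 0.027)/√(0.91 × 0.9919) = 0.287.

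**The case against.** The strongest reply is that this is one loose clause in an exploratory section. Mediation is not among the hypotheses in section 1.2, the sample-size basis in section 3.4 or the confirmatory models in section 5.1. The causal phrase describes SEM in general. Section 1.1.1 is balanced, since it cites a negative finding. In section 1.1.3 the word impact is tied to variation between countries, not to the SEM. All of this is fair. It limits the reach of the point, but the clause still gives the method, for this analysis, a property that the design cannot provide.

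Three stronger readings should be resisted.
- **That a reversed order gives the same significant indirect effect.** The effects are equal only in special cases, such as a pure chain or r_XM and r_MY of equal absolute size. Step 6 shows wide divergence. The article does not assume a zero direct path: section 5.1.1 tests acceptance as a predictor of depression and stress.
- **That leaving out competing orders or sensitivity analyses is itself an error.** A condensed article may leave such detail to a fuller plan, and Fig 1 is not shown. The fault is what the text states.
- **That mediation should not be claimed if a reversed order is also significant.** When the planned pure chain is true, the reversed order is nearly always significant as well, so correct conclusions would be barred. With a direct path, the result turns on relative link sizes and not on direction.

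That each participant is measured once is inferred from sections 1.1.3 and 2.1; the article does not say so outright.

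**Conclusion.** The point holds in limited form. The causal purpose that section 5.6 gives to SEM is not supported by the design in sections 1.1.3, 2.1 and 2.4. At the minimum sample size, a significant planned indirect effect is likely under a reversed pure chain (about 86% to over 99%) and far from rare when distress drives both other variables (about 24% to 54%). It cannot establish that camouflaging causally mediates.

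The lack of identification follows from saturation and the design and needs no assumed numbers. The percentages rest on the assumed links, n = 286, linear relations and, for these two ranges, the two-path test; the planned bootstrap points the same way.

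A reader might infer that the study's main results are compromised. They are not: the four confirmatory regressions and the MANOVA do not depend on this analysis. Nor does the check show that mediation is absent.

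**What to change.** 1. In section 5.6, delete the clause saying that SEM is used to infer causal relationships. Report the result as an indirect association that is consistent with the assumed direction but is not evidence for it.
2. Add a sensitivity analysis giving the mediator-outcome residual correlation at which the indirect effect becomes zero. It addresses confounding only, not time order.
3. Optionally, report the reversed order (mental health, then camouflaging, then acceptance) descriptively. State that its significance or non-significance does not identify direction, and do not use it to decide whether the planned result may be reported. A model in which mental health drives both other variables has no indirect effect through camouflaging to report.
4. Put the same limit on the word impact in section 1.1.3.

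No extra participants or measures are needed. The cost is a wording change, a little extra analysis and a weaker permitted claim.

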#### 1.2.2. Comparing levels of autism acceptance, camouflaging and mental health across cultures

Finally, we will separate participants into groups based on their country and use a between-subjects multivariate analysis of variance (MANOVA) to explore participants’ experiences of autism acceptance, camouflaging, and levels of depression, anxiety and stress (dependent variables) across these countries (independent variable). We predict that there will be differences in the level of autism acceptance across countries. In addition, we aim to explore whether there are any differences in the level of camouflaging and mental health difficulties across countries.

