### 5.3. Inference criteria (optional)

For our regression analyses, to account for the four tests we will use a p < .0125 significance threshold to determine whether to accept or reject the null hypothesis. For our MANOVA, we will use a p = .05 significance threshold.

In our analyses, Bayes Factors (BF_01_) may be reported, which provide a ratio of the likelihood for the observed data under the null hypothesis compared to the alternative hypothesis [101]. For all Bayesian analyses, we will follow the classification scheme in JASP outlined by Lee and Wagenmakers [102]: BF_10_ values between one and three will be considered as weak evidence, between three and ten as moderate evidence and greater than ten as strong evidence for the alternative hypothesis.

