Finally, in order to compare the strength of the relationships between our dependent variables across genders, we will complete an additional exploratory MANOVA using the standardised residuals discussed above. This is useful because the strength of the relationships between our dependent variables could vary across genders: it could be the case, for instance, that there is a stronger relationship between autism acceptance and camouflaging in autistic women than autistic men, thus explaining the higher rates of camouflaging displayed by autistic women [40–48]. In addition, it could be that there is a weaker relationship between camouflaging and mental health difficulties in autistic men since they more frequently report positive consequences of camouflaging [38].

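### A MANOVA on standardised residuals compares average levels, so it cannot show whether relationships differ in strength between countries or genders

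*Protocol article*

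**What the plan says.** In section 5.6 of the protocol article the authors plan standardised residuals for three relationships (acceptance with mental health, acceptance with camouflaging, camouflaging with mental health), calculated over the whole sample. After that, "we will complete an exploratory MANOVAs in which we will compare the standardised residuals across countries". The stated purpose is to "compare the strength of these relationships in each of the countries by comparing the levels of unexplained variance following regression analyses". The motivating example is about moderation: in collectivist cultures it may be that "camouflaging accounts for a smaller portion of variance in mental health".

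The section then repeats the method for gender, again as a comparison of strength of relationship: "we will complete an additional exploratory MANOVA using the standardised residuals discussed above". The examples there are also about moderation, namely a stronger acceptance–camouflaging link in women and a weaker camouflaging–mental health link in men.

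For this question the section names no interaction term, no multi-group model and no comparison of group slopes.

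**The concern.** The method and the stated inference do not match. A MANOVA tests whether groups have the same mean vector. Applied to signed residuals, it asks whether some groups lie systematically above or below the pooled regression line. The authors want to know whether the line is steeper, or the fit tighter, in some groups than in others.

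Two errors follow. A real difference in slope can go undetected. A difference in level that the predictor does not account for will be reported as a difference in the strength of association. The second error is likely on the protocol's own terms, because section 1.2.2 states: "We predict that there will be differences in the level of autism acceptance across countries". Section 1.1.1 also cites indications of more camouflaging in women.

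**Working it through.** The plan gives no figure to reproduce. The check concerns what the test estimates, first by algebra and then by simulation.

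**Inputs from the protocol article.** At least 286 participants (3.3); seven named countries (1.1.3); at least 30 per country in the country comparisons (3.4.2); for alpha, "For our MANOVA, we will use a p = .05 significance threshold" (5.3). **Assumed, not in the document:** all slopes and shifts, balanced groups (7 × 41 = 287 for country, 2 × 143 = 286 for gender), and simple regressions pooled over all participants.

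**Step 1: the mean residual.** Let group g follow y = a_g + b_g·x + error, and let the pooled line be a + b·x. Then

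mean residual in g = (a_g − a) + (b_g − b)·mean(x_g).

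Standardising divides by a common scale and does not alter the comparison.

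- Slopes 0 in three countries and 0.6 in four, intercepts equal, predictor means 0: b = (3×0 + 4×0.6)/7 = 0.343. The slope deviations are −0.343 and +0.257, but each is multiplied by 0, so every group's mean residual is 0 and there is nothing to detect.
- Equal slopes, two of seven countries shifted by 0.5 SD: a = 2×0.5/7 = 0.143. Mean residuals are 0.357 and −0.143, although the slopes are identical.

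**Step 2: fitting within each country instead.** Least-squares residuals average exactly 0 within each fit, so all group means would be 0 and the MANOVA would have nothing to test.

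**Step 3: unexplained variance.** In group g the spread about the pooled line is σ_g² + (b_g − b)²·Var(x_g). This is a variance, which a comparison of mean residuals does not address. It also does not rank strength: with gender slopes −0.6 and 0 and pooled slope −0.3, the extra term is 0.09·Var(x) in both groups.

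**Step 4: what the joint MANOVA becomes.** Take one acceptance score A, one camouflaging score C and one mental health score M. The three residuals are, up to constants, M − c1·A, C − c2·A and M − c3·C. They are linear combinations of A, C and M, with determinant c2·c3 − c1. Unless that is 0, the transformation is invertible. MANOVA statistics are unchanged by such a transformation, so this test is the MANOVA on the raw levels of A, C and M. In simulated data the two Pillai traces agreed (for example 0.2133 and 0.2133).

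**Step 5: rejection rates at alpha 0.05.** ANOVA on one pooled residual against the F test of the group × predictor interaction, 2,000 replicates:

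| Scenario | Residual test | Interaction test |
|---|---|---|
| 7 countries, slopes 0 (three) vs 0.6 (four) | 5.4% | 99% |
| 7 countries, slopes 0.1 vs 0.5 | 4.8% | 75% |
| 7 countries, equal slopes, two shifted 0.5 SD | 86% | 4.9% |
| Gender, slopes 0.1 vs 0.5 | 5% | 95% |
| Gender, equal slopes, 0.4 SD shift | 95% | 5% |

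Three-residual MANOVA (Pillai) against the interaction F test for acceptance and mental health, 4,000 replicates:

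| Scenario | Residual MANOVA | Interaction test |
|---|---|---|
| Equal slopes, equal levels | 4.7% | 4.4% |
| Country slopes −0.7 to 0, equal levels | 6.5% | 100% |
| Same, constant error variance | 6.3% | 99.9% |
| Equal slopes, intercepts ±0.4 SD | 100% | 5.2% |
| Equal slopes, only acceptance means differ, ±0.5 SD | 100% | 4.9% |
| Gender, slopes −0.6 vs 0 | 4.3% | 100% |
| Gender, equal slopes, 0.5 SD intercept difference | 100% | 5.1% |

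The row in which only acceptance means differ is the kind of difference that section 1.2.2 predicts. Step 4 explains the result: the joint test contains the acceptance level itself.

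**The case against.** **The analyses are exploratory.** True. The hypotheses in section 1.2 do not include moderation, and the confirmatory regressions, the main MANOVA and the sample size do not depend on this step. That limits the damage, but the label does not make the test answer the question it is given.

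**Slope differences can enter mean residuals.** True where predictor means also differ between groups. One such scenario gave 99.95% rejection for the MANOVA. But the same predictor means with equal slopes gave 100%, so a rejection says nothing specific about slope. The accurate description is that level and slope are confounded, not that slope never matters.

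**Reference to unexplained variance might mean absolute or squared residuals.** The text does not say so, and the reading does not rescue the plan. With country slopes from −0.7 to 0, absolute residuals detected a difference in 57.6% of runs when total variance was held equal across groups, and in 5.4% when error variance was constant.

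**Pooled fitting is a reading of the text.** It is the natural one, since residuals are calculated for all participants. The alternative, fitting by country, fails as shown in step 2.

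**The effect sizes and balanced groups are assumed.** True. The rates illustrate how the test behaves; they are not forecasts for this study. Likewise, only a level difference that the predictor does not explain shifts the residual mean for that relationship.

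**Conclusion.** The concern holds. As written, the country and gender residual MANOVAs test conditional level differences and are interpreted as tests of strength of association. With equal levels, the simulated residual tests rejected at 4.3% to 6.5% even though slopes differed, while the interaction test detected the same differences in 75% to 100% of runs. With equal slopes and shifted levels, the residual tests rejected in 86% to 100% of runs, while the interaction test stayed near 5%.

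The direction of these results follows from the algebra and does not depend on the assumed effects; the exact rates do. Misinterpretation requires level differences to exist, and the protocol predicts them for acceptance. Both moderation questions in section 5.6 currently lack a valid test. Nothing outside the exploratory section is affected.

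**What to change.** Delete the residual MANOVAs from section 5.6. For each relationship, fit one regression with group main effects, the predictor, and the group-by-predictor interaction, where group is country or gender. Test the interaction block with

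F = [(RSS without interaction − RSS with interaction)/(G − 1)] / [RSS with interaction/(N − 2G)],

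where G is the number of groups. With one predictor and no further covariates this has 6 and 273 degrees of freedom for seven countries of 41, and 1 and 282 for two genders of 143. Report each group's slope with a 95% CI. The intervals matter because power was only about 75% for country slopes of 0.1 versus 0.5.

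For country, keep the minimum of 30 participants that section 3.4.2 already sets. For gender, state which categories are compared. A multi-group SEM comparing constrained with free paths is a reasonable alternative, since SEM is already planned for the mediation analyses.

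The cost is a change of wording in section 5.6. No new data are needed, and the software stays the same.
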